**Figure 2 F2:**
[figure not shown]
CIs for different estimates of sensitivity for 150, 200 and 250 cases of SBD. SBD, significant bowel disease.

**Figure 3 F3:**
[figure not shown]
CIs for different estimates of NPV for 400 500 and 600 negative cases of SBD from 1000 samples. NPV, negative predictive value; SBD, significant bowel disease.

### Stool sample analysis

Stool samples will be analysed for traces of haemoglobin in the faeces using a HM-JACKarc. Participants samples will be defined as having suspected SBD if the value is >10
μ
 gHb/g faeces. Any previous FIT results collected to triage patients can be sourced from patient records if the test is <4 weeks before their colonoscopy or CTC.

### Urine VOC analysis

Participants will be asked to collect duplicate urine samples in universal sterilin pots. Urine samples will be transported to the analysis site using dry ice to maintain the cold chain. All urine samples will be analysed using the ‘electronic nose’^16^ technique. Briefly, this technique enables separation of VOCs between disease groups based on chemical fingerprint pattern rather than specific chemical analysis. This allows screening of populations rapidly using chemometric data analysis (information extracted from chemical systems) and receiver operator curves (ROC) to distinguish one population from another, with ROCs being used to measure the appropriate thresholds to be set to distinguish samples as having SBD. A sample which has a ROC with an area under the curve of 0.63 or greater will be defined as having suspected SBD.

A subset of 100 urine samples will also be analysed using a gas-chromatography mass spectroscopy system. This technique separates complex mixtures of chemicals based on their interaction with a retentive layer, resulting in chemicals eluding out of the gas-chromatography at different times. These individual chemicals are then ionised and the mass of the resultant fragments measured. The analysis will be split into two stages. First, a subset of SBD positive and SBD negative samples will be screened to identify up to 8 VOCs that are prominent in SBD positive samples. Once identified, a headspace gas chromatography/mass spectrometry method will be developed to detect, separate and quantify the target VOCs selected in stage one within the remaining samples. This method will highlight whether specific VOCs present more frequently in SBD positive samples.

### Adoption of study due to COVID-19 pandemic: remote delivery

In order to continue recruiting through the COVID-19 pandemic, an innovative study design was adopted whereby participant involvement shifted to an entirely remote approach. This allowed the study to continue recruiting through the peak waves of COVID-19 when many other studies were forced to temporarily pause.^20^

### Reference test

The reference test is the final report from the colonoscopy or CTC examination and confirmatory histology report. Biopsies are required as per national guidance^5^ in the investigation of participants with lower GI symptoms even in the absence of macroscopic abnormalities. Those who perform the reference test will have no knowledge of the results of the index tests and vice versa.

### Data management

Data from the study will be stored on an online validated Good Clinical Practice (GCP) compliant electronic data capture (EDC) system. Individual user access will be provided only to members of the research team who require it for their role. No personal data will be uploaded to the EDC. Participant identification codes will be used to ensure pseudoanonymisation. Following the resolution of queries, the database will be locked and exported to the trial statistician for analysis. Access to the final trial dataset will only be made available to those who require it for the analysis.

### Primary outcome analysis

The primary outcome is diagnostic accuracy (sensitivity, specificity, NPV and positive predictive value (PPV)) of the dual index test FIT and VOC analysis. The ‘or’ rule will be utilised for the primary analysis whereby a FIT result of >10 µgHb/g faeces OR a VOC result with predicted probability >0.63 implies that the participant is suspected of having SBD and needs to be referred for colonoscopy or CTC. We will report 2×2 tables of test accuracy of the dual test by the reference standard (final report from the colonoscopy examination and confirmatory histology report of SBD which is either colon cancer, colorectal adenomas or IBD), alongside summary measures of sensitivity, specificity, NPV and PPV, and their 95% CIs. These test accuracy estimates will be used in the economic model.

We will analyse the combined FIT+VOC test results as both parallel (results from both tests are interpreted in combination) and serial testing (VOC analysis only performed if FIT is negative). The ‘or’ rule will be considered in the interpretation of both parallel and serial tests where the diagnosis is positive when either test is positive, and negative when both results are negative. In the serial test, if the FIT is positive, then the diagnosis is positive. If FIT is negative we will use the result from VOC analysis and if that is positive then the diagnosis is positive. Mathematically, both methods should give the same diagnostic results but will make a difference in the economic model.

### Secondary outcome analyses

Secondary outcomes include: ROC of FIT plus VOC to develop an optimum thresholds for SBD detection; sensitivity, specificity, PPV and NPV estimates and their corresponding 95% CI for each individual condition of SBD (CRC, colorectal adenomas and IBD) by each individual test and combination rules; compliance rates (return of samples); the types of SBD and microscopic colitis, and the number of cases missed by CTC, FIT and VOC analyses; potential number of avoidable colonoscopies and CTCs in patients without SBD; total NHS and personal social services costs and total quality of adjusted life years (QALY) associated with each option. To find the optimal thresholds of FIT and VOC we will first plot the ROC curves of both tests individually to find the individual optimal thresholds (the one that gives the greatest specificity while achieving 97% sensitivity). Second, we will plot combinations of the two tests in the ROC space and similarly, choose the combination of thresholds which has greatest specificity while achieving the required 97% sensitivity to avoid colonoscopy. The combined thresholds of FIT and VOC in the ROC space are calculated by combining every unit of FIT (from 10 to 120µgHb/g faeces) with every unit of the predicted probability of VOC (from 0.63 to 1). Both the ‘or’ and ‘and’ rules will be explored when combining the FIT and VOC results to define a case as either SBD positive or SBD negative. If both tests are in discordant then the diagnosis is negative. For each of the thresholds that we derive from the ROC curves, we will also report the NPV estimates. This will produce an overestimate of test accuracy, which we will use as a sensitivity analysis in the economic model, as a more optimistic assumption to demonstrate the range of uncertainty.

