**Methods and analysis:**

This is a multicentre, prospective diagnostic accuracy study evaluating whether stool FIT plus urine VOC compared with stool FIT alone improves detection of SBD in patients referred for colonoscopy or CTC due to persistent lower gastrointestinal symptoms. To ensure SBD is not missed, the dual test requires a high sensitivity, set at 97% with 95% CI width of 5%. Our assumption is that to achieve this sensitivity requires 200 participants with SBD. Further assuming 19% of all participants will have SBD and 55% of all participants will return both stool and urine samples we will recruit 1915 participants. The thresholds for FIT and VOC results diagnosing SBD have been pre-set. If either FIT or VOC exceeds the respective threshold, the participant will be classed as having suspected SBD. As an exploratory analysis we will be testing different thresholds. The reference comparator will be a complete colonoscopy or CTC. Secondary outcomes will look at optimising the FIT and VOC thresholds for SBD detection. An economic evaluation, using a denovo decision analytic model, will be carried out determine the costs, benefits and overall cost-effectiveness of FIT +VOC vs FIT followed by colonoscopy.

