## Methods and analysis

### Study design and procedures

This is a multicentre (UK only), prospective diagnostic accuracy study, sponsored by the University Hospitals Coventry & Warwickshire (UHCW) to compare dual testing of stool FIT plus urine VOC markers compared with stool FIT alone in the detection of SBD. Participants will be recruited when referred to secondary care for investigation of lower bowel symptoms, after informed consent is received. Inclusion criteria will be: patients referred non-urgently or urgently (fulfilling the national criteria for referral—NICE NG12)^18^ with lower GI symptoms and determined by the overseeing clinician to require colonoscopy or CTC; minimum age of 18; able to provide informed consent, and have the ability to return both stool and urine samples. Exclusion criteria are those who are pregnant. Participants will be recruited over the phone or face-to-face during a clinic visit which precedes their colonoscopy or CTC. Participants will be asked to provide a stool sample and urine sample at least 24 hours before commencing their bowel cleansing medication. Stool samples will be collected at home by the participants using FIT collection kits and posted directly to the analysis site. If the participant has already completed a FIT during their referral pathway, we will use this data if the time between the FIT and their colonoscopy is less than 4 weeks, otherwise we will request that the participant to provide another FIT. Urine samples will be returned to hospitals and frozen at −80°C pending future analysis. Urine samples can either be collected during a clinic visit that precedes their colonoscopy or CTC, or collected at the home of the participant and brought back by the participant. We will aim for the time between the urine sample being produced and the urine sample being frozen at −80°C to be less than 4 hours, otherwise we will ask participants to freeze their urine samples in their home freezer. For the purposes of the economic analysis, a subset of participants (20% of total) undergoing colonoscopy or CTC will also be asked to complete questionnaires at five time points surrounding their examination. This will help determine the disutility and costs associated with undergoing colonoscopy or CTC, which will be used as inputs in the economic model (see section Economic Evaluation below). Figure 1 shows a participant flow diagram once enrolled in the REducing Colonoscopies in patients without significant bowEl DiseasE (RECEDE) study.

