### Sample size calculation

To replace colonoscopy—the current gold standard for diagnosing bowel conditions—and/or CTC, FIT and VOC analysis requires a very high sensitivity to avoid false negatives. High specificity is also desirable, to reduce false positives. Based on our previous study, the sensitivity of FIT and VOC analysis to detect CRC was 97%, comparable to colonoscopy. Therefore, the sample size was determined to achieve a sensitivity of at least 97% with a 95% CI width of 5% (Zhou-Li method^19^ as described in box 1). The required number of participants with SBD to achieve this sensitivity is 200. Figure 2 shows CIs for different observed sensitivity cases of SBD (150, 200, 250). Figure 3 shows the widths of the CI limits are narrower and wider when the observed sensitivity is above or below 97%,^13^ respectively. This sample size is also robust to negative predictive value (NPV), an outcome that is of interest as a high NPV suggests that participants without SBD would avoid having colonoscopy examination. Assuming the prevalence of SBD in the study population is 19%, then 1053 participants are required. Based on our previous study,^13^ the return rate of both stool and urine samples that are eligible for analysis is about 55% resulting in a total required sample size of 1915 participants across multiple UK sites within a 24-month period.

Box 1Sample size determination based on CI methodThe Zhou Li CI is 
$\left(\frac{e^{LL}}{1+e^{LL}},\frac{e^{UL}}{1+e^{UL}}\right)\left(\frac{e^{LL}}{1+e^{LL}},\frac{e^{UL}}{1+e^{UL}}\right)$
 where 
$LL=ln\left(\frac{\bar{S}\bar{e}}{1-\hat{Se}}\right)-\frac{1}{\sqrt{n\hat{Se}(1-\hat{Se})}}g^{-1}(z_{1-\alpha /2})$
, 
$UL=ln\left(\frac{\bar{S}\bar{e}}{1-\hat{Se}}\right)-\frac{1}{\sqrt{n\hat{Se}(1-\hat{Se})}}g^{-1}(z_{\alpha /2})$
, 
$g^{-1}(x)=-\sqrt{n}\left(\frac{6}{\hat{\gamma }}\right)\left\{{\left[1-\frac{\hat{\gamma }}{2}\left(\frac{x}{\sqrt{n}}-\frac{\hat{\gamma }}{6n}\right)\right]}^{1/3}-1\right\}$
and
$\hat{\gamma }=\frac{1-2\bar{S\bar{e}}}{\hat{Se}(1-\hat{Se})}$

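### Cases missed by CTC cannot be counted where CTC is itself the reference test, and the primary 2×2 table uses a narrower reference standard than the rest of the protocol

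*Protocol article*

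**What the plan says.** The reference standard appears in three places in the Protocol article.

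- Abstract, Methods and analysis: "The reference comparator will be a complete colonoscopy or CTC".
- Reference test: "The reference test is the final report from the colonoscopy or CTC examination and confirmatory histology report". The section adds that biopsies are required "in the investigation of participants with lower GI symptoms even in the absence of macroscopic abnormalities".
- Primary outcome analysis, where the 2×2 tables are defined: "final report from the colonoscopy examination and confirmatory histology report of SBD". CTC is not named.

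Under Study design and procedures, participants are those "determined by the overseeing clinician to require colonoscopy or CTC". The article describes no paired examination, no colonoscopy after a negative CTC and no follow-up for SBD that was missed.

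Secondary outcome analyses then lists "the number of cases missed by CTC, FIT and VOC analyses", which places CTC beside the two index tests.

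**The concern.** A miss can be counted only against a separate and better source of truth. FIT and VOC have one, the reference examination. CTC has none in participants for whom it is the reference examination. A count near zero would then reflect the design and could be read as evidence that CTC misses nothing.

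The same gap reaches the primary outcome. SBD that CTC does not show enters the table in the no-SBD column. If FIT and VOC are both negative, a false negative of the dual test is recorded as a true negative. If either is positive, a correct detection is recorded as a false positive. The protocol itself says that "FIT and VOC analysis requires a very high sensitivity to avoid false negatives", so false negatives are the errors that matter most here. The four accuracy measures also feed the economic model.

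Finally, CTC is imaging and yields no tissue, so CTC alone cannot meet a requirement for histology. Read literally, the primary analysis section gives CTC-only participants no qualifying reference result. Whether they enter the primary denominator depends on which section is followed.

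**Working it through.** **The plan's own figures.** The Box 1 interval at n = 200 and sensitivity 0.97, with a square root in the denominator of the skewness term, runs from 0.9387 to 0.9877, a width of 0.049. This agrees with the stated 5%. Then 200/0.19 = 1052.6, rounded up to 1053, and 1053/0.55 = 1914.5, rounded up to 1915. The sample size reproduces and is not in question. At 97%, 200 × 0.03 = 6 false negatives carry the result.

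**What can be observed, by examination received.**

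| Participant had | Source of truth | Can a CTC miss be seen? |
|---|---|---|
| Colonoscopy only | colonoscopy and histology | not applicable |
| CTC only | CTC report | no |
| CTC, then colonoscopy with histology | colonoscopy and histology | yes, but this group is neither planned nor representative |

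Histology after a positive CTC can expose a CTC false positive. It says nothing about a negative CTC.

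**Effect on sensitivity.** The article gives neither the CTC share nor a CTC miss rate for SBD, so the following inputs are assumptions:

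- 200 true SBD cases and true dual-test sensitivity of 94% in both modality groups, that is 188 index-positive and 12 index-negative cases;
- CTC share c of 10–30%;
- CTC miss rate r of 10–30%.

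Cases unseen at CTC: m = 200 × c × r, from 2 to 18. If k of these are index-negative,

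observed sensitivity = (188 − (m − k)) / (200 − m).

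*Independent misses.* k = 0.06m, so observed sensitivity = (188 − 0.94m)/(200 − m) = 0.94 for every m. Sensitivity is unbiased, but 0.94m index-positive cases (1.9 to 16.9) become false positives among the 1053 − 200 = 853 without SBD.

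*Misses falling first on index-negative cases.* The CTC group contains 12c index-negative cases, so k cannot exceed 12c. For r of at least 10%, m exceeds 12c and the upper limit is k = 12c.

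| CTC share | Miss rate | m | k | Observed sensitivity, upper limit |
|---|---|---|---|---|
| 10% | 10% | 2 | 1.2 | 187.2/198 = 94.5% |
| 10% | 30% | 6 | 1.2 | 183.2/194 = 94.4% |
| 20% | 10% | 4 | 2.4 | 186.4/196 = 95.1% |
| 20% | 30% | 12 | 2.4 | 178.4/188 = 94.9% |
| 30% | 10% | 6 | 3.6 | 185.6/194 = 95.7% |
| 30% | 30% | 18 | 3.6 | 173.6/182 = 95.4% |

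*Misses falling only on index-positive cases.* k = 0, and sensitivity falls slightly: 176/188 = 93.6% at m = 12 and 170/182 = 93.4% at m = 18.

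*At the planned 97%.* The 6 index-negative cases replace the 12, so k = 6c. The highest value is again at a 30% share and 10% miss rate: m = 6, k = 1.8, (194 − 4.2)/194 = 97.8%.

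**The case against.** The strongest reply is that this is loose drafting. The article often writes colonoscopy for both examinations. The Economic evaluation section, for example, introduces participants scheduled for either one and then names most questionnaire time points after colonoscopy alone. The omission of CTC in the primary analysis section may be the same habit. That is plausible, and only that section differs on modality, so a reader should not infer three different primary denominators. But that sentence defines the primary table, and the article does not say it is shorthand.

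A reader might also infer that the CTC count must be zero or is undefined. The documents do not support this, because nothing excludes a participant having both examinations, and a later colonoscopy could reveal a CTC miss. What stands is that such a count would be partial and selected.

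A reader might further infer inflation of several points, for instance from 94% to 182/188 = 96.8% (m = 12, k = 6) or 179/182 = 98.4% (m = 18, k = 9). The first needs 6 of the 12 index-negative cases among 40 CTC cases: index sensitivity of at most 34/40 = 85% there, against at least 154/160 = 96.25% with colonoscopy. The second needs at most 51/60 = 85% against at least 137/140 = 97.9%. Nothing in the documents suggests such a gap.

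The Introduction describes a combined FIT and VOC sensitivity of 97% as similar to colonoscopy and CTC. That concerns CRC only. If a 3% CTC miss rate nevertheless held for all SBD at a 20% share, m would be 1.2 and observed sensitivity at most 188/198.8 = 94.6%.

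Lastly, tables by modality are often left to an analysis plan, and their absence from an article would not by itself be a finding. The finding is the conflicting reference definitions and an outcome the stated design cannot deliver. The tables are part of the remedy.

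**Conclusion.** The point holds. As described, the design cannot show CTC misses in CTC-only participants, and the reference standard for the primary table is narrower than the one stated elsewhere. Both follow from the text, together with the plain fact that imaging yields no biopsy.

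The effect on sensitivity is possible but of unknown size. There is no bias if CTC misses are independent of FIT and VOC. Under the assumed ranges, with equal sensitivity of 94% in both groups, the upper limit is about 95.7%, or 1.7 points, roughly a third of the planned 5-point interval width. If misses fall on index-positive cases, the bias is slightly downward. The documents support the statement that pooling can hide false negatives, not that it will. The issue should be corrected, but it does not undermine the design.

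**What to change.** 1. Use one reference definition in the Abstract, Reference test and Primary outcome analysis sections. State whether CTC-only participants enter the primary 2×2 table, and reconcile the histology wording with CTC.
2. Drop CTC from the missed-cases outcome, or restrict it to participants with an independent colonoscopy and histology result and label the count as partial.
3. Report the primary 2×2 table by reference modality, with colonoscopy-verified participants as a sensitivity analysis of the primary result.
4. Report IBD accuracy and the microscopic colitis count in participants with histology. For microscopic colitis the plan lists types and counts, not accuracy, so no accuracy estimate is called for.

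The cost is text edits and one further table from data already recorded. No change in who receives which examination is needed. The downside is precision: if a quarter of SBD cases had CTC only, 150 of 200 would remain, and the Box 1 interval at 97%, computed as above, would widen from 0.049 to 0.057.

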## Introduction

There is currently a disparity between demand and available resources for colonoscopies and CT colonography (CTCs) within the National Health Service (NHS). Before the COVID-19 pandemic, around 300 000 patients were being referred annually to NHS trusts suspected of having colorectal cancer (CRC) and this number was rising.^1^ Most patients referred with suspected CRC are offered an invasive colonoscopy or CTC examination, but only 30% of these participants have significant bowel disease (SBD).^2^ SBD is defined as CRC, adenomatous polyps or inflammatory bowel disease (IBD).^3^ The remaining 70% have a normal examination with 30% of those having functional conditions such as irritable bowel syndrome (IBS).

Set against this there will remain a capacity shortfall for colonoscopies and CTCs for the foreseeable future. This limits capacity of the NHS to extend CRC detection within the Bowel Cancer Screening Programme (BCSP) or to investigate those who present through the emergency department. The imbalance between capacity and demand, coupled with a lack of an accurate triage test makes it difficult for the NHS to stratify patients who present with bowel symptoms to those most at risk of SBD. In the COVID-19 era, faecal immunochemical testing (FIT) is being introduced to triage patients who present with lower gastrointestinal (GI) symptoms.^4^ However, almost all patients still receive a colonoscopy or alternative colonic imaging at some time and the optimum threshold for FIT has yet to be determined. The National Institute for Health and Care Excellence (NICE) have recommended 10
μ
gHb/g faeces,^5^ whereas the BCSP have set a cut-off of 120
μ
gHb/g faeces.^6^ Even at the lower threshold some SBD cases can be missed.^2 7 8^ Previous data have shown that FIT alone (at a threshold of 7
μ
gHb/g faeces) has a sensitivity of 80%, 53% and 86% for CRC, adenomatous polyps and IBD respectively.^2^ A lower FIT threshold may reduce the number of false negatives but it will increase the number of unnecessary colonoscopies and CTCs in patients with no abnormalities (false positives). Moreover it will always miss cases of SBD where there is no bleeding, and a high proportion of malignant tumours never bleed.

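### The joint threshold search starts at the primary cut-offs and only goes up, so the 'and' rule is not expected to reach 97% sensitivity, the 'or' rule can do so only if the primary result already has, and the sentence on discordant results needs limiting to 'and'.

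*Protocol article*

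**What the plan says.** The Primary outcome analysis section of the protocol article fixes the main rule: "The ‘or’ rule will be utilised for the primary analysis whereby a FIT result of >10 µgHb/g faeces OR a VOC result with predicted probability" above 0.63 counts as suspected SBD. The same section defines 'or' as positive if either test is positive and negative only if both are negative.

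The Secondary outcome analyses section then sets up a two-step search. Step one plots each test's own ROC curve and takes the cut-off with the greatest specificity at 97% sensitivity; no range is given. Step two combines the tests by "combining every unit of FIT (from 10 to 120µgHb/g faeces") "with every unit of the predicted probability of VOC (from 0.63 to 1"). The aim is to "choose the combination of thresholds which has greatest specificity while achieving the required 97% sensitivity to avoid colonoscopy". On the rules, the section says "Both the ‘or’ and ‘and’ rules will be explored when combining the FIT and VOC results", and the next sentence reads "If both tests are in discordant then the diagnosis is negative". The section expects the resulting accuracy to be overestimated and uses it as an optimistic sensitivity analysis in the economic model.

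The Introduction states that FIT alone at 7 µgHb/g "has a sensitivity of 80%, 53% and 86% for CRC, adenomatous polyps and IBD respectively". For VOC alone it gives 80%, 92% and 86%, without stating a cut-off.

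**The concern.** The criterion is a minimum sensitivity of 97%, but the grid moves only in the direction that lowers sensitivity. Its lowest corner, FIT 10 with VOC 0.63, is the primary cut-off pair, and every other point is stricter on at least one test. The search can trade surplus sensitivity for specificity. It cannot recover sensitivity that is missing at the corner.

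Optimum thresholds are a listed secondary outcome and feed an economic scenario. If the grid holds no qualifying pair, the section gives no rule for what to report, and widening the grid at that stage would be a choice made after seeing the data. The 'and' rule is the one suited to the Introduction's aim of better specificity in patients with slightly raised FIT and negative VOC, and it is the rule least likely to return anything.

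The discordance sentence follows directly on one that names both rules. Coded for both, it makes 'or' the same as 'and'.

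**Working it through.** **Inputs.** 200 SBD cases, 97% sensitivity with a 95% CI width of 5%, 19% prevalence and 55% return of both samples (Sample size calculation); primary cut-offs FIT >10 and VOC >0.63 (Primary outcome analysis); grid FIT 10 to 120 and VOC 0.63 to 1 (Secondary outcome analyses); single-test sensitivities for colorectal cancer, adenomatous polyps and IBD of 80%, 53% and 86% for FIT at 7, and 80%, 92% and 86% for VOC (Introduction).

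**The plan's own figures reproduce.** At a sensitivity of 0.97 and n = 200, the Zhou-Li interval is 4.9 percentage points wide, in line with the stated 5%. Then 200/0.19 = 1052.6, giving 1053, and 1053/0.55 = 1914.5, giving 1915. The sample size is not in question.

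**Step 1: direction of the grid.** Raising either cut-off can only move cases from test-positive to test-negative. Under both rules, sensitivity on the grid is therefore greatest at (10, 0.63).

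**Step 2: 'and' rule.** Se(and) ≤ min(Se_FIT, Se_VOC), and Se_FIT at any cut-off of 10 or more ≤ Se_FIT at 7.

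| Condition | FIT at 7 | VOC | Ceiling for 'and' |
|---|---|---|---|
| Colorectal cancer | 80% | 80% | 80% |
| Adenomatous polyps | 53% | 92% | 53% |
| IBD | 86% | 86% | 86% |

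No mix of the three conditions exceeds 86%. An observed 97% of 200 is 0.97 × 200 = 194 cases. At a true 86%, P(X ≥ 194 | n = 200) = 1.5 × 10⁻⁷.

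**Step 3: 'or' rule.** A pair qualifies only if the corner, which is the primary result, shows at least 194 of 200.

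| True sensitivity of primary rule | P(X ≥ 194 of 200): a pair exists | Search empty |
|---|---|---|
| 95% | 0.12 | 0.88 |
| 96% | 0.31 | 0.69 |
| 97% (planned) | 0.61 | 0.39 |
| 98% | 0.89 | 0.11 |
| 99% | 0.996 | 0.004 |

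**Step 4: where the truth might lie.** The planned 97% is a colorectal cancer figure, while the target condition is all SBD. If the two tests err independently (an assumption), the Introduction's figures give:
- colorectal cancer: 1 − 0.20 × 0.20 = 96.0%
- adenomatous polyps: 1 − 0.47 × 0.08 = 96.2%
- IBD: 1 − 0.14 × 0.14 = 98.0%

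So any mix lies between 96% and 98%, which covers the middle rows of the table.

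**Step 5: small simulation.** Assumed: independent tests, sensitivity 80% (FIT) and 85% (VOC), specificity 75% and 70% at the primary cut-offs, 200 participants with SBD and 853 without. In 15 data sets the printed grid held a qualifying 'or' pair in 9 and a qualifying 'and' pair in none. With both ranges started at 0, each rule had one in all 15. That last result required only a specificity above zero, so it shows that a pair exists, not that it is useful.

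**Step 6: discordance.** For a pair with one positive and one negative test, the 'or' rule of the primary section gives positive, and the discordance sentence gives negative. If the sentence covers both rules, 'or' reduces to 'and' and Step 2 applies to the whole search.

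**The case against.** A reader might infer that the search as a whole cannot work. The article does not support that. When the primary result is at least 97%, the upward 'or' grid does what is asked of it, and at the planned sensitivity that is more likely than not (0.61). Quoting only true values of 95% to 97% would be one-sided, since the sample size section plans for at least 97%.

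Nor can it be said that lower cut-offs are never examined. The single-test ROC step has no stated range; only the joint grid is bounded. The FIT bounds also have a visible source: 10 and 120 are the two national cut-offs named in the Introduction, and searching upward suits the stated interest in specificity.

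It is tempting to say that the discordance sentence abolishes the 'or' rule and with it the gain from VOC. It more naturally describes 'and', because otherwise exploring both rules would be pointless and the primary section's definition would be overridden. This stands as an objection to the strong reading. The sentence is still unqualified and could be coded either way.

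Two further cautions hold. The 'and' ceiling comes from sensitivities in earlier studies and is not a mathematical necessity; it would fail if both tests were at least 97% sensitive at the primary cut-offs, which the Introduction's figures contradict. And a wider grid does not guarantee a useful 'and' rule: as the FIT cut-off approaches the point where everyone is positive, 'and' approaches VOC alone.

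**Conclusion.** The point holds for the joint grid. On the article's own figures the 'and' half is capped at about 86% and is not expected to return a pair. The 'or' half returns one only if the primary result already meets 97%; it is empty with probability 0.88 down to 0.004 over true sensitivities of 95% to 99%, and 0.39 at the planned value. These probabilities assume 200 evaluable SBD cases and a binomial count. The discordance sentence, read literally, contradicts the definition of 'or'.

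The consequence is limited. The abstract calls testing other thresholds exploratory, and the result feeds only an optimistic economic scenario, while the main economic inputs come from the primary estimates. The primary analysis and the sample size are unaffected. This should be corrected, but it does not threaten the trial's main result.

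**What to change.** 1. Extend the joint grid downward for both rules, with FIT from the lowest reportable assay value and VOC predicted probability from 0. Keep the present upper ends and leave the primary cut-offs unchanged.
2. Reword the discordance sentence so that discordant results are negative under 'and' and positive under 'or'.
3. State in advance what happens if no pair on the present grid reaches 97%: say so, and report the sensitivity-specificity frontier together with the highest-sensitivity pair on that grid (for 'or', the primary rule itself). Report specificity beside every selected pair, so that a pair reaching 97% only by calling nearly everyone positive is seen for what it is.

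The cost is changed loop limits and a few sentences, with no new data. The larger search adds some optimism to an estimate the article already describes as too favourable, and a feasible 'and' pair may have little specificity; both should be noted beside the result. The change should be made before the data are examined.
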